### Allocation, randomization, blinding and compliance

Participants will be randomized to treatment with melatonin or placebo in a ratio of 1:1 according to a list of computer-generated random numbers in permuted blocks ranging from 8 to 12. This strategy decreases the risk of unblinding of participants in one particular block if, for some reason, the group membership of one of its members is disclosed. The list will be generated and maintained by an independent biostatistician.

The pharmacy will dispense melatonin or placebo. Melatonin and placebo will be administered as oral capsules that have the same size, weight, color, texture and taste. The active medication will consist of 3 mg melatonin. These will be manufactured in batches every 12 months with 6-monthly stability testing performed for weight, disintegration, impurities and appearance. The pharmacy will be responsible for dispensing all study medications, which will be included on the patient medication chart as per usual hospital practice. Unblinding will only occur once the final endpoint of interest is collected from the last participant in the trial. Compliance will be encouraged through a telephone call to each participant 2 days prior to his or her scheduled surgery date. Participants will be reminded to take their tablets and will be asked to bring the remainder into hospital for use following their surgery. Participants will be given ten tablets to allow for the possibility of surgery being postponed once they have commenced taking the trial medication. We will record all incidences where participants take extra tablets beyond the scheduled seven. Treatment adherence will be determined by the systematic review of medication charts upon discharge and by pill count. Use of sedative/psychotropic medications outside of the study protocol will also be recorded.

### Data collection and management

Data collection will be paper-based and subsequently entered into a secure, password-protected database. Paper files will be kept in a locked filing cabinet in the principle investigator’s office and stored for a minimum of 5 years following completion of the trial.

### Statistical methods

We will analyze and store the data using reliable statistical software (Stata, StataCorp, College Station, TX, USA). Baseline data will be compared using descriptive statistics, Student *t* tests for normally distributed continuous variables, the Mann-Whitney test for ordinal variables and Pearson’s chi-square statistic for categorical variables. The primary outcome analysis will be intention-to-treat and will use multilevel logistic regression of panel data (xtlogit). This approach to the analysis of the data allows for the inclusion of all available information and for the investigation of interactions between terms (such as intervention and time). A similar approach will be used to analyze other binary outcomes (e.g., use of psychotropic medication). We will use multilevel mixed models to investigate changes in scores of the MDAS and TICS-m (continuous variables). All probability tests will be two-tailed and will be declared as significant when *p* < 0.05.

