**Fig. 1 Fig1:**
[figure not shown]
Meta-analysis of available clinical trials. Forest plot showing the published clinical trials of melatonin for the prevention of delirium (primary outcome of incident delirium). The meta-analysis shows a slight benefit for melatonin over placebo although small sample size and study heterogeneity prevents firm conclusions from being drawn

In a trial of acutely ill medical in-patients aged 65 and older, Al-Aama and colleagues randomly allocated 72 patients to melatonin and 73 to placebo [31]. Patients consumed 0.5 mg of melatonin or placebo every night for 14 days, or until discharge. Delirium was diagnosed according to the Confusion Assessment Method (CAM) [32]. Melatonin use was associated with a lower risk of delirium (12 % versus 31 %, *p* = 0.014; NNT = 6), with an odds ratio (OR) adjusted for dementia and comorbidities of 0.19 (95 % CI 0.06 to 0.62). These differences remained significant when patients with prevalent delirium on admission were excluded (19.2 % in the placebo and 3.6 % in the melatonin group, *p* < 0.02).

More recently de Jonghe and colleagues completed a multicenter, placebo-controlled clinical trial in 378 patients undergoing hip surgery [33]. Participants received 3 mg of melatonin for 5 days starting within 24 hours of admission. The authors found no difference in the incidence of delirium between the melatonin (55/186, 29.6 %) and placebo (49/192, 25.5 %) groups (difference 4.1 %, 95 % CI −0.05 to 13.1), but reported that a smaller proportion of participants in the melatonin group experienced a long-lasting episode of delirium (>2 days) (25.5 % versus 46.9 %, *p* = 0.02). Lastly, Hatta and colleagues conducted a small trial of the melatonin agonist, ramelteon (8 mg per day for 7 days) in 67 acutely unwell medical patients [34]. They reported a significant decrease in the incidence of delirium in those taking ramelteon as compared to placebo (3 % versus 32 %, *p* = 0.003; NNT = 4). The forest plot presented in Fig. 1 summarizes the efficacy data of these trials.

The results of these trials suggest a potential role for melatonin in preventing and treating delirium in older adults, although conflicting results, methodological issues (e.g., absence of a placebo-control group) and differing patient populations prevent firm conclusions from being drawn and generalized.

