### Objectives

The primary outcome of interest for this study is the difference in the incidence of delirium (as determined by the CAM and *Diagnostic and Statistical Manual of Mental Disorders, version 5* (DSM-5) criteria) between the placebo and melatonin groups within 7 days following cardiac surgery. Secondary outcomes of interest include the difference between groups in the severity and duration of delirious episodes, hospital length of stay and referrals to mental health services during the admission. In addition, we will assess for differences in mood and anxiety symptoms and cognitive performance at discharge and at 3 months after surgery.

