#### Establishing the presence of delirium

The CAM will be used to establish the presence of delirium. The first assessment will take place in the pre-assessment clinic or hospital ward prior to the surgery (usually a week before but this can vary) and then daily, beginning 1 day post surgery and continuing for up to 7 days or until discharged (whichever comes first). The CAM was developed in 1988–1990 and is a widely used and well-validated screening tool for delirium, with sensitivity of 94 % (95 % CI 91–97 %) and specificity of 89 % (95 % CI 85–94 %) [37]. A trained research nurse will rate the scale on the basis of a standardized interview with the patient that includes a brief cognitive assessment. Case notes and nursing staff reports will be reviewed as part of the assessment. The diagnosis of delirium will be confirmed in consultation with an experienced psychogeriatrician ([name] or [name]). The CAM rates nine areas (acuity, attention, thought organization, level of consciousness, orientation, memory, perception, psychomotor tempo and sleep), but delirium is only diagnosed when there is evidence of acute onset, inattention, fluctuating mental state and either disorganized thinking or disturbed consciousness. The CAM has been successfully adapted for use in the intensive care setting [38]. The rating of the CAM takes about 10 minutes to complete.

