### Sample size

The primary outcome of the proposed trial is the development of delirium within 7 days of surgery. We based our sample size on the trial of Al-Aama and colleagues [31]. They reported a 15.6 % absolute reduction (19.2 % versus 3.6 %, *p* < 0.02) in the incidence of delirium in their sample. Assuming a 15.6 % absolute risk reduction in our patients with a conservative 25 % incidence of delirium in the control group and an incidence of 9.4 % in the intervention group, we will require 91 participants per group (182 participants in total) to detect a difference of this magnitude with a power of 80 % and a two-sided alpha of 0.05. After allowing for a conservative loss to follow-up of 15 % [31], we calculated that we will need to recruit 210 participants (105 per group). A defined secondary outcome for this trial is cognitive performance 1 week and 3 months after surgery. A study with 100 participants per group at the 3-month follow-up will have 81 % power to declare as significant between group difference of 2 points in the change from baseline score of the TICS-m (1 versus 3 points, SD 5). A change of less than 2 points would be of uncertain clinical significance.

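### The only primary analysis named, a panel-data xtlogit, does not estimate the stated primary outcome, per-participant incidence of delirium within 7 days

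*Protocol article*

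**What the plan says.** The outcome is defined consistently. Objectives: "The primary outcome of interest for this study is the difference in the incidence of delirium" between the arms within 7 days of surgery. Sample size: "The primary outcome of the proposed trial is the development of delirium within 7 days of surgery". The trial is sized on that outcome, from a "conservative 25 % incidence of delirium in the control group" and 9.4% in the intervention group, giving 91 per group for 80% power at two-sided 0.05.

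The analysis is defined in Statistical methods: "The primary outcome analysis will be intention-to-treat and will use multilevel logistic regression of panel data (xtlogit"). The reasons given are that the approach uses all the available information and permits "investigation of interactions between terms (such as intervention and time"). No other primary analysis is named.

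The only repeated delirium measure is the Confusion Assessment Method (CAM). It is given daily, "beginning 1 day post surgery and continuing for up to 7 days or until discharged (whichever comes first"), and also at baseline and 3 months (Table 1). Objectives lists duration separately: "Secondary outcomes of interest include the difference between groups in the severity and duration of delirious episodes".

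**The concern.** A result that is one binary value per participant leaves no panel, no within-person level and no time term. The named model therefore needs several rows per participant, and the daily CAM is the natural source. No sentence reduces those rows to ever delirious, stops them at first onset, or derives a 7-day incidence from the fitted model.

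A model of status at each assessment responds to how long episodes last as well as to whether they occur, so the primary test would mix the primary outcome with a secondary one. The headline odds ratio would also be conditional on a participant-specific random effect, and could not be read as an effect on incidence.

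The article itself shows that the two can part. Under Existing preliminary data, the earlier 3 mg hip-surgery trial found no reduction in incidence (29.6% melatonin, 25.5% placebo), yet "a smaller proportion of participants in the melatonin group experienced a long-lasting episode of delirium (>2 days"), 25.5% versus 46.9%.

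**Working it through.** **1. Reproduce the sample size.** Inputs from Sample size: p0 = 0.25, p1 = 0.094, difference 0.156, two-sided alpha 0.05, power 0.80. The pooled proportion is 0.172.

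n = [1.960·√(2·0.172·0.828) + 0.842·√(0.25·0.75 + 0.094·0.906)]² / 0.156² = (1.046 + 0.439)² / 0.02434 ≈ 90.7, so 91 per group.

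This matches the protocol. Power at 91 per group is 80.1%, and at the 105 recruited per group it is 85.5%. The calculation is an ordinary comparison of two per-participant proportions.

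**2. Effect on the outcome's own scale.** Incidence odds ratio = (0.094/0.906) / (0.25/0.75) = 0.1038/0.3333 = 0.31.

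**3. What the panel model returns.** Simulation with 91 per arm and seven daily CAMs each. Assumptions: an episode is either short (1–2 days) or long (3–5 days), with no early discharge. The model is a random-intercept logit with treatment only, tested by likelihood ratio. The comparator is the two-proportion test of ever delirious. The long-episode shares of 46.9% and 25.5% come from the earlier 3 mg trial as cited in the article. The other shares and all durations are assumptions.

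| Incidence, placebo vs melatonin | Long share, placebo vs melatonin | Median panel OR | Panel test rejects | Two-proportion test rejects |
|---|---|---|---|---|
| 25% vs 9.4% | 46.9% vs 46.9% | 0.12–0.13 | 81.1% | 80.4% |
| 25% vs 9.4% | 46.9% vs 25.5% | 0.12 | 83.6% | 79.7% |
| 25% vs 9.4% | 25.5% vs 46.9% | 0.21 | 70–74% | 79.9% |
| 25% vs 9.4% | 46.9% vs 100% | not tabulated | 61–65% | about 80% |
| 25% vs 25% | 46.9% vs 46.9% | 1.03 | 5.9% | 4.4% |
| 25% vs 25% | 46.9% vs 25.5% | 0.80 | 7.3% | 5.5% |
| 25% vs 25% | 90% vs 10% | 0.41 | 32.8% | 4.9% |

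Ranges span repeated runs. With 1,000 replicates, the Monte Carlo standard error near 80% is √(0.8·0.2/1000) = 1.3 percentage points.

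**4. Reading.** The panel odds ratio differs from the incidence odds ratio whenever either incidence or duration differs between arms. Power and error rate move materially only when duration also differs. Power is lost when the remaining melatonin episodes are longer. Rejection without an incidence effect rises markedly only under extreme duration differences.

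**The case against.** **The model is partly inferred.** Statistical methods says neither random-effects nor daily CAM, and an article may leave row construction to the analysis plan. A panel cut at first onset would target incidence. This stands as a limit on certainty, but not as an answer. The article names the model and gives its reasons, and using all the information with intervention-by-time terms points away from stopping at onset. A fixed-effects xtlogit could not estimate the main effect of a treatment that is constant within a participant, so random effects is the natural reading. Whether the baseline and 3-month CAMs enter is not stated. If they do, the mismatch with a 7-day outcome grows.

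**The practical effect is small at the design point.** This stands. With equal durations the two tests have the same power, and 0.13 against 0.31 is partly a difference of scale between a conditional and a participant-level odds ratio.

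Three stronger readings are tempting, and the documents do not support them:

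- *A five-day episode counts five times a one-day episode.* That would hold for a pooled count of days. In a random-intercept model each further positive day adds less. Under the assumed duration mix, a five-day episode contributes about twice what a one-day episode does to the treatment score, and the step from none to any delirium is the largest.
- *The model would declare benefit if melatonin merely shortened episodes, as in the earlier 3 mg trial.* At that trial's shares with equal incidence, rejection is about 7%. The 32.8% figure needs shares of 90% versus 10%, which have no source in the article.
- *The trial is underpowered.* The losses need longer episodes on melatonin, the opposite of the pattern in that earlier trial.

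**Conclusion.** The point holds as a mismatch between outcome and analysis. The plan defines and sizes the trial on per-participant 7-day incidence, but its only named primary analysis estimates a conditional odds of being delirious at an assessment, which also depends on duration. The sample size arithmetic is not at fault.

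The size of the consequence depends on duration. At the planned effect, the reported odds ratio would be about 0.13 instead of 0.31, and a reader could take it for a far larger effect on incidence. Power stays near 80% with equal durations and falls to about 70–74% or 61–65% in the two adverse cases. False claims of an incidence effect are a minor risk at the duration shares that the article cites.

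The mismatch itself rests on reading the panel as repeated CAM rows with a random participant effect. The numbers rest further on the assumed episode lengths, a treatment-only model and full seven-day follow-up.

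**What to change.** In Statistical methods, make the primary analysis an intention-to-treat comparison of the proportion of participants with any confirmed delirium from surgery to day 7, with one binary value per participant. Logistic regression on arm would serve, reported with an absolute or relative effect and its 95% CI; the choice of effect measure is secondary to matching the outcome. Keep xtlogit of the repeated CAM as a secondary analysis of daily prevalence and time course, and state which assessments enter it.

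The cost is wording only. The daily CAM already supplies the data, the 91 per group already fits this analysis, and Trial status says that recruitment has not begun.

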Various factors increase the risk of delirium, including age, pre-existing cognitive impairment, disruption of the circadian rhythm, dehydration, malnutrition, and certain medications [16]. Major cardiac surgery increases the risk of delirium, with critical contributing factors including the type of surgery, use of hemofiltration, medications administered, length of surgery, time on bypass, high transfusion requirement, postoperative hypertension, patient’s age and whether the surgery was elective [7]. Some of these risk factors are amenable to change, whilst others (e.g., age) are not.

Current approaches to the prevention of delirium in hospitalized patients consist of both non-pharmacological and pharmacological approaches, of which the former are arguably more effective [17]. Non-pharmacological approaches involve addressing multiple risk factors in a systematic manner together with education and environmental manipulation, although only relatively modest reductions in delirium incidence are usually attainable [18]. Pharmacological approaches may include treatment with antipsychotic drugs, cholinesterase inhibitors, hypnotics, anti-inflammatory drugs and gabapentin [19], but supportive evidence of efficacy is not compelling. In addition, all of these agents carry a relatively high risk of adverse effects.

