#### Measuring morbidity and lifestyle

Alcohol abuse or dependency: the AUDIT is a 10-item questionnaire designed to screen for excessive drinking. It takes 2 minutes to complete, with scores of 15 or greater indicating harmful alcohol use or dependency [36]Medical morbidities, medications and lifestyle: we will collect information about demographics, lifestyle (smoking, alcohol use, body mass index), common medical conditions diagnosed by a doctor, and medications used (including use of illicit substances). This questionnaire takes approximately 5–10 minutes to completeDetails of surgery: we will record the type of surgery and total length of surgical procedure including duration on bypass (if applicable)Medications: we will record participants’ medications on admission and discharge. We will also record the use of all psychiatric medications during hospitalizationReferral to mental health or geriatric services during admission will be recordedLength of stay (LOS): we will record total hospital stay duration and intensive care unit (ICU) length of stay in hours for participants discharged alive from hospitalDestination post discharge: we will record destination post discharge for all participants and, for the purposes of analysis, will group them into “discharge to usual place of residence” versus “discharge to other places.” Participants who die following cardiac surgery will form a separate groupCognition: this will be measured with the TICS-m. The TICS-m is a brief, widely used telephone assessment instrument with good reliability and validity to screen for dementia and cognitive impairment in older people [40]. It can be rated in person or by telephone. It consists of 13 items measuring various aspects of cognitive function yielding a total score of 50. Scores ≤27 indicate the presence of clinically significant cognitive impairment. Cognitive function will be measured at baseline, discharge and 3 months after surgery. The TICS-m was chosen to allow us to assess participants’ cognition 3 months after surgery in the comfort of their own homes. We deliberately chose this approach to reduce participant burden and improve study retention. In addition, many Western Australian patients live in country areas so that in-person attendance would be difficultDepressive and anxiety symptoms: we will measure depressive and anxiety symptoms at baseline, discharge and at 3 months with the Hospital Anxiety and Depression Scale (HADS) [41]. This is a self-report scale of 14 items in total that gives sub-scores for both depression and anxiety

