## Discussion

Delirium is a major issue for the medical community and is associated with universally poor outcomes for patients, their families and the health care system. Delirium is particularly problematic in surgical populations and may complicate up to 42 % of patients undergoing major cardiac surgery. Identification and management of sufferers is often complex and many individuals are missed. Prevention of this common condition is, therefore, essential. This trial will determine if melatonin is able to reduce the incidence and duration of delirium following cardiac surgery and also reduce the burden of other associated factors such as cognitive decline, hospital length of stay and anxiety and depressive symptoms.

The design of this trial has strengths and weaknesses that merit comment. It has not yet been established what dose of melatonin may be optimal for the prevention or treatment of delirium. The trials conducted to date have utilized a variety of doses ranging from 0.5 to 5 mg [30, 31, 33] and one that used 8 mg of the melatonin agonist ramelteon [34]. The trial by de Jonghe and colleagues showed the 3-mg dose used in the study to be both well-tolerated and safe [33], as did another trial in tracheostomized intensive care patients that additionally showed that 3 mg melatonin successfully increased blood levels 1000-fold [42]. A number of other trials have confirmed the safety and tolerability of a 3-mg dose in populations with varying medical morbidities and age ranges [43–46]. We will exclude participants with cognitive impairment, given the possible difficulties with consent and the ability to follow the trial protocol. We understand, however, that this may reduce the overall incidence of delirium in our sample, as pre-existing cognitive impairment is a strong predictor of delirium.

This trial will be restricted to adults aged 50 and older because the incidence of delirium is higher in later life. We will also exclude participants undergoing emergency surgery because of the ethical requirements for recruitment and informed consent. The study will be limited to participants with sufficient English skills to be able to participate in the assessments and complete the study questionnaires. All of these factors could potentially decrease the generalizability of our findings.

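### The primary model names no baseline covariates and allocation names no stratification factor, although age and baseline cognition are identified as delirium predictors and collected at baseline

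*Protocol article*

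**What the plan says.** **Primary model.** Under Statistical methods, the Protocol article names intention-to-treat multilevel logistic regression (xtlogit) and adds: "This approach to the analysis of the data allows for the inclusion of all available information and for the investigation of interactions between terms". Intervention and time follow as an example of such terms. The section neither lists baseline covariates nor says that the model is unadjusted.

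**Allocation.** Under Allocation, randomization, blinding and compliance, participants are randomised 1:1 "according to a list of computer-generated random numbers in permuted blocks ranging from 8 to 12". No stratification factor is named.

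**Predictors.** The Background lists age and pre-existing cognitive impairment among general risk factors. For cardiac surgery it lists, among others, the type of surgery, and it ends with "age and whether the surgery was elective". The Discussion states that "pre-existing cognitive impairment is a strong predictor of delirium".

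**What is collected, and when.** Table 1 places demographics and the TICS-m at baseline. Age (50 or over) and TICS-m (19 or less excluded) are also eligibility criteria, so both must be known before a participant is allocated. Table 1 places surgery details at discharge or day 7. Elective or semi-elective status determines the recruitment route but is not listed as a recorded variable.

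**Baseline comparison.** "Baseline data will be compared using descriptive statistics", and also by t, Mann-Whitney and chi-square tests.

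**Cognitive range enrolled.** The Discussion says that people with cognitive impairment will be excluded. The eligibility criteria exclude a dementia diagnosis or a TICS-m of 19 or less. Under Measuring morbidity and lifestyle, scores of 27 or less "indicate the presence of clinically significant cognitive impairment".

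**The concern.** The article identifies predictors of its own primary outcome and measures at least two of them in everyone before allocation, but nothing in the design or analysis shown uses them. Two things are at stake.

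- **Precision.** For a binary outcome, adjusting for a prognostic baseline variable generally raises the power of the treatment test and narrows the interval for a standardised risk difference. How much depends on how prognostic the variable is.
- **Credibility after a chance imbalance.** With few events, an uneven split on age or cognition would raise the question whether the result reflects treatment. An adjustment fixed in advance answers that question. One chosen after seeing the baseline table does not.

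The only handling of baseline differences described is significance testing. Under randomisation those tests examine a null hypothesis that is true by design, so a small p-value only flags chance. It gives no sound basis for choosing covariates.

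**Working it through.** **1. Reproduce the planned sample size.** The inputs come from the Sample size section. The endpoint is binary ("The primary outcome of the proposed trial is the development of delirium within 7 days of surgery"). The rates are p1 = 0.25 ("with a conservative 25 % incidence of delirium in the control group") and p2 = 0.094, with two-sided alpha 0.05 and 80% power. The mean rate is (0.25 + 0.094)/2 = 0.172.

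n per group = [1.96 √(2 × 0.172 × 0.828) + 0.8416 √(0.25 × 0.75 + 0.094 × 0.906)]² / 0.156² = 90.7, rounded up to 91.

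This matches the article's 91 per group (182 in total), with power 80.1%. The formula uses no covariates, so the planned power does not depend on adjustment.

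**2. Expected events.** 91 × 0.25 + 91 × 0.094 = 22.75 + 8.55 = 31.3.

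- Treatment plus two single-parameter covariates: 31.3/3 = about 10 events per parameter.
- Treatment plus four: 31.3/5 = about 6.

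**3. What adjustment would add.** The article gives no prognostic strength, so it is assumed. The simulation used 91 per arm, marginal rates held at 25% and 9.4%, and one standard-normal baseline risk score with log-odds slope b per SD. The treatment effect was tested by likelihood ratio in a logistic model for any delirium, with about 5,000 trials per setting for power and 3,000 under the null.

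| b | AUC of score | Power without score | Power with score | Gain (points) |
|---|---|---|---|---|
| 0 | 0.50 | 82.5% | 82.2% | -0.3 |
| 0.5 | 0.64 | 83.2% | 84.0% | 0.8 |
| 0.8 | 0.71 | 81.8% | 84.8% | 3.0 |
| 1.0 | 0.74 | 81.7% | 86.4% | 4.7 |
| 1.5 | 0.82 | 82.0% | 89.9% | 7.9 |

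The likelihood-ratio test runs slightly above the formula's 80.1%, so the comparison to read is across each row. The Monte Carlo standard error of one power figure is √(0.82 × 0.18/5000) = 0.5 points. Type I error was 4.9% to 5.8% across settings, with and without the score.

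**4. Two covariates, as in the fix.** A second simulation used two independent predictors, each with an assumed odds ratio per SD of 1.5, 2.0 or 2.5. Power rose from 82% to 83%, from 81% to 85% and from 83% to 88%. The standard error of the standardised risk difference fell by 3%, 6% and 10%. With 1,500 trials per setting, each power figure has a Monte Carlo standard error of about 1 point. The gains fit those in step 3.

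**5. How often chance imbalance arises.** For a binary factor of prevalence q with 105 per arm and no stratification on it, the standard error of the between-arm difference is √(2q(1 − q)/105).

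- q = 0.3: 0.063, so P(gap above 10 percentage points) = 11%.
- q = 0.5: 0.069, so the probability is 15%.

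The prevalences are assumptions.

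**6. The cognitive range.** Exclusion at 19 or less, set beside impairment at 27 or less, leaves people without a dementia diagnosis who score 20 to 27 eligible, though the article classes those scores as impaired. Part of the range of the one predictor called strong therefore stays in the trial. How many people fall in it is not stated.

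**The case against.** The strongest objection is that silence is being read as a decision. This is a journal article, and neither the full protocol nor an analysis plan is shown. A covariate list is commonly left to those documents, and intervention and time are given only as an example. This stands to the extent that a reader might infer that the primary model has been fixed as unadjusted; the text does not say so. It is accurate only that the article names the model and names no covariate for it.

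A reader might also infer that the trial loses power or is exposed to bias. The documents do not support that. The 91 per group meets 80% power without covariates, an unadjusted randomised comparison is valid, and its type I error already allows for chance imbalance. Permuted blocks without stratification are likewise acceptable.

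It is tempting to call all the listed factors strong predictors already recorded in everyone, and to adjust for four of them. Only cognitive impairment is called strong, and its lowest range is cut off at entry. Surgery details are scheduled at discharge, and elective status is not a listed variable. Four covariates are heavy for about 31 events.

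Finally, the size of the gain is assumed, and both simulations fit a single any-delirium endpoint, not a daily panel model. Both limits stand. The single endpoint was used because the sample size is built on it.

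What survives is that age and baseline TICS-m are named as predictors, measured before allocation and unused in what is shown. Using them costs almost nothing even if they prove uninformative.

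**Conclusion.** The point holds as an inexpensive improvement to the analysis, not as an error that threatens the primary result. Prespecified adjustment for baseline TICS-m and age would add roughly 0 to 8 power points at 91 per arm: about 1 to 5 points if the covariates together reach an AUC of 0.64 to 0.74, about 8 at an AUC of 0.82, and nothing if they carry no information (82.5% against 82.2%). These figures rest on assumed prognostic strength, the planning rates of 25% and 9.4%, and a single binary endpoint. The gain in credibility does not depend on those strengths: an imbalance above 10 percentage points on a given common binary factor would arise in about 11% to 15% of randomisations.

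The baseline significance tests and the wording on cognitive impairment are real but minor. Neither changes the primary result.

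**What to change.** - **Primary model.** State that the primary logistic model adjusts for baseline TICS-m and age, both continuous, or confirm that the analysis plan already does so. Report a standardised risk difference for delirium within 7 days.
- **Elective status.** Add it only if it is recorded at allocation. Keep the set short in view of about 31 expected events.
- **Baseline table.** Present descriptive statistics only and remove the significance tests.
- **Cognitive impairment.** Reconcile the Discussion with the Eligibility criteria and the TICS-m description, so that the status of participants scoring 20 to 27 is clear.

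The cost is wording. TICS-m and age are already needed for eligibility, no extra participants are required, and the article states that recruitment has not begun. Adding elective status would need one recorded item at allocation.
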